### Randomization

Randomization in a 1:1:1 ratio will occur after participants are recruited but before they complete a baseline survey to ensure that group assignment does not influence the answers given. We will stratify random assignment by age (under 25 or over 25), sex, marital status (married/cohabiting or unmarried), low CD4 count (below 200 or above 200), and viral load (detectable or undetectable). Stratified randomization is achieved by generating a separate block for each combination of covariates after identifying which clients fall into each block. We will then randomize treatment assignment within each block. We will use the *randtreat* package in Stata15 for the randomization procedure.

All clients recruited will complete the baseline survey approximately 2–3 months after recruitment. The client will be informed of their assignment to either one of the two intervention arms or the control group after completing the baseline survey.

Participants cannot be blinded to their treatment status and neither can interviewers. Interviewers are not blinded to treatment status when they read a MEMS cap. The data analyst who will conduct the impact analysis will be blinded to treatment assignment.

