### Design

The study has two intervention arms and a control arm. Both intervention arms will offer lottery-based incentives but with different conditions. We will collect treatment adherence data continuously for 2–3 months prior to the intervention, for 24 months after the intervention begins, and for 12 months after the intervention ends for all participants using MEMS caps. We will acquire routine viral load measures for all participants throughout the study, which will be recorded roughly every 12 months as per clinic and Ugandan Ministry of Health guidelines. We will also conduct a baseline survey and follow-up surveys every 6 months for 24 months for all participants. Figure 1 gives the timing of study activities.

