#### Baseline survey and randomization

When a client returns for their next scheduled clinic visit after recruitment (after about 2–3 months), we will conduct the baseline survey, reveal their treatment assignment to either the control or one of the two intervention groups, and begin the intervention. We will exclude all clients who did not open the MEMS cap for at least 30% of the days during the pre-baseline period as consistent use of the MEMS cap is essential for participation in the study. This second visit will (just as the first one) coincide with a scheduled clinic visit so that participants do not have to come to the clinic solely to participate in study activities.

The baseline survey contains information about:
demographics and socioeconomic status, including age, gender, education, relationship status, employment type and status, income, housing, economic shocks, and household compositionmedical history, including history of opportunistic infections, health-seeking behavior, current medications and length of time on current drug regimen, and WHO HIV disease stage, some of which will be taken from their medical recordsphysical symptoms and side effects, for example, respondents will be asked how “bothersome” and “disruptive” (in separate items) any symptoms perceived to have been caused by their medication in the past month have beenreasons for non-adherence or failure to seek care; we will use an 11-item module regarding reasons for non-adherence developed by the AIDS Clinical Trials Group that we slightly modified to fit the Ugandan context that asks participants to indicate whether listed items were reasons for not taking their medication in the previous month or seeking care, such as “when the drugs make you feel bad,” or “when your daily routine is interrupted,” or “lacked resources”

We use the Intrinsic Motivation Inventory to examine participants’ subjective experiences of taking medications [47]. The survey will also collect information on behavioral economics biases, such as present bias or risk preferences.

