### Sample size and power

We have calculated the size of effects that our sample will be able to detect with 80% power (two-tailed test) with regard to outcomes at months 12 and 24, and 10% attrition every year (we observed 5% attrition over 20 months in our previous studies so this is a conservative estimate). For the primary outcome of viral suppression, we use a conservative estimate of 70% of clients in the control group showing suppression, based on discussions with the Mildmay team. Our sample size of 110 participants in each of the three arms (total *n* = 330) will be able to detect a 7 percentage point difference for joint comparison of T1 and T2 against the control group at month 12, and about an 8.5 percentage point difference between the two intervention arms (a subgroup analysis). The corresponding differences at month 24 are 8 and 9 percentage points, respectively. These are considered small effect sizes (Cohen’s *d* of between .15 and .185), which we will be able to detect. For adherence, in our previous study we observed mean adherence rates of ~75% as measured by MEMS caps. Our sample size of 110 in each of the intervention arms and the control group will provide sufficient power to detect about a 6.5 percentage point difference in mean adherence between the two intervention arms (combined) and the control group. To test for differences in adherence between the two intervention arms, our study is powered to detect about a 7.5 percentage point effect as measured by MEMS caps. Again, this means we will be able to detect small effects. The corresponding differences we will be able to detect at month 24 are about 7 and 8 percentage points, respectively. Our main econometric models will include covariates that will improve precision. Therefore, these minimum detectable effects reported above are likely upper bounds.

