##### Estimating impact on measured adherence over time

We will have a consecutive real-time measure of adherence for the duration of the study, which allows us to study adherence over time. To estimate the impact of the interventions on adherence over time, we will use the following ordinary least squares model:
5$$ {y}_{it}={\beta}_0+\sum \limits_{t=1}^{24}{\lambda}_t\left(T{1}_{it}\times {\mathrm{Month}}_t\right)+\sum \limits_{t=2}^{24}{\delta}_t\left(T{2}_{it}\times {\mathrm{Month}}_t\right)+\sum \limits_{t=1}^{24}{\mathrm{Month}}_t+{\epsilon}_i $$

where *y*_*it*_ represents the proportion of the prescribed bottle openings that were actually opened by individual *i* in month *t*. In this model, the *λ*_*t*_’s represent the impact of T1 at study month *t* and the *δ*_*t*_’s represent the impact of T2 at study month *t*.

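### Eq. 5 starts the T2-by-month terms at month 2 but the T1 terms at month 1: probably a misprint, contradicted by the protocol's own definition of the coefficients, and affecting month 1 only

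*Protocol article*

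**What the plan says.** Under 'Estimating impact on measured adherence over time', the protocol article introduces Eq. 5 with "we will use the following ordinary least squares model". The right-hand side has an intercept, T1-by-month interactions with coefficients λ_t for t = 1 to 24, T2-by-month interactions with coefficients δ_t for t = 2 to 24, and month terms for t = 1 to 24. It has no main effect for T1 or T2.

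The text then interprets the coefficients in parallel wording: the λ_t's "represent the impact of T1 at study month" t, and the δ_t's "represent the impact of T2 at study month" t. Neither statement is restricted to particular months.

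On timing, 'Baseline survey and randomization' says that at the baseline visit staff will "reveal their treatment assignment to either the control or one of the two intervention groups, and begin the intervention". The 'Design' section says that adherence data are collected continuously "for 24 months after the intervention begins, and for 12 months after the intervention ends for all participants using MEMS caps".

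**The concern.** The formula and the sentence that explains it disagree. The sentence promises a T2 effect for every study month, but the formula contains no δ_1. With no T2 main effect in the model, nothing else can absorb T2's month-1 mean. T2 participants in month 1 therefore have the same regressor values as control participants in month 1 and become part of the reference group.

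The design gives no reason to treat the two arms differently. Both learn their assignment and start at the same visit, and all arms contribute electronic adherence data from then on. T2 participants are told their adherence rule when they learn their assignment, so month 1 is already an incentivised month for them.

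What is at stake is the first point of each arm's trajectory. T2's would be missing, and T1's could be measured against a mixture of control and T2. Literal code would give no obvious warning of this.

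**Working it through.** The protocol states no figure that depends on Eq. 5, so there is none to reproduce. The check is on the model itself.

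**Inputs**
- Summation limits: T1 from 1 to 24, T2 from 2 to 24, month from 1 to 24 (Eq. 5).
- Allocation: "Randomization in a 1:1:1 ratio will occur after participants are recruited" ('Randomization').
- Arm size: "Our sample size of 110 participants in each of the three arms" ('Sample size and power').
- Control level for the illustration: 75%, because "in our previous study we observed mean adherence rates of ~75% as measured by MEMS caps" ('Sample size and power').
- Illustrative effect: 6.5 points. This is the protocol's detectable difference in mean adherence for the combined intervention arms against control. Using it as a month-1 effect is my assumption. Effects of 5 and 10 points are added to show a range.

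**Step 1. Expected values in month 1 under the printed model**
- T1: β_0 + Month_1 + λ_1
- T2: β_0 + Month_1
- Control: β_0 + Month_1

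T2 and control share one fitted value, so least squares sets it to their pooled mean:

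λ_1 = mean(T1) − [n_C × mean(C) + n_T2 × mean(T2)] / (n_C + n_T2)

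Subtracting the control mean throughout:

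E[λ_1] = true T1 effect − true T2 effect × n_T2 / (n_T2 + n_C)

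With 110 per arm the weight is 110/220 = 1/2, so the bias is minus half the true T2 month-1 effect.

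**Step 2. Numbers (percentage points, month 1)**

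| True T1 | True T2 | λ_1 as printed | λ_1 with T2 sum from t = 1 |
|---|---|---|---|
| 6.5 | 0 | 6.5 − 0 = 6.5 | 6.5 |
| 6.5 | 6.5 | 6.5 − 3.25 = 3.25 | 6.5 |
| 10 | 10 | 10 − 5 = 5 | 10 |
| 5 | 10 | 5 − 5 = 0 | 5 |

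A least-squares fit to noise-free data with 110 participants per arm gave these same values. Starting the T2 sum at t = 1 recovered both arms' month-1 effects exactly.

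**Step 3. Other months.** From month 2 on, each month has its own month term and both interactions. In the fits, λ_2 and δ_2 equalled the true effects under both versions.

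**Step 4. Does omitting T2-by-month 1 serve identification?** Two data sets were considered.
- Months 1 to 24 only. The printed design has 1 + 24 + 23 + 24 = 72 columns and rank 71. The corrected design has 1 + 24 + 24 + 24 = 73 columns and rank 72. Each is short by one, because the 24 month indicators sum to the intercept. Removing an interaction does not cure that.
- Pre-intervention months added. Both designs have full rank (72 of 72 and 73 of 73), and the printed version gives the same λ_1 values as in Step 2.

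So the omission solves no collinearity problem. Nor is it normalisation to a reference month, because T1 keeps its month-1 term.

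**The case against.** The strongest reply is that this is a typographical slip and that the intent is already clear from the next sentence. That largely stands: the text defines δ_t for study month t without exception, and a misprint is the most likely explanation. The equation is also schematic in other ways. It prints no coefficient on the month terms and keeps an intercept alongside all 24 month indicators, so any analyst must interpret it before coding. The harm arises only if this one limit is taken literally. It remains a wrong statement in the stated model, and correcting it silently would depart from the published equation.

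Several stronger readings are tempting but unsupported.
- A reader might infer that T1's month-1 effect is necessarily biased. It is not: the bias is zero if T2 has no effect in that month.
- A reader might infer that a stated aim of the trial is compromised. The protocol's interest is in T1 against T2 overall ('Discussion' and the abstract). The T2-minus-T1 contrast is written out under the viral suppression model, and nowhere is an early or month-1 comparison named as an aim.
- A reader might suppose that month 1 is when a new incentive acts most. The documents give no month-1 effect, and T2's first draw comes only at the next scheduled visit, roughly 2 to 3 months later.
- A reader might take 6.5 points as an expected month-1 effect. It is a detectable difference for the combined arms, borrowed here only to give scale.

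**Conclusion.** The inconsistency is real and minor. If Eq. 5 is coded as printed, δ_1 is not estimated, and λ_1 equals the true T1 month-1 effect minus half the true T2 month-1 effect. The factor of one half assumes equal numbers of control and T2 participants with month-1 data, as 1:1:1 allocation implies. The size in points depends on an unknown T2 month-1 effect: nil if that effect is nil, and a halving of T1's coefficient (3.25 instead of 6.5) if both arms are assumed to gain 6.5 points.

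Only one of the 24 T1 coefficients can be distorted and one T2 coefficient is missing, in a supplementary trajectory model. Eqs. 1 to 4, which estimate the effects on viral suppression and average adherence, do not use these terms, and the sample-size figures do not depend on them.

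**What to change.** Change the lower limit of the T2 sum in Eq. 5 from t = 2 to t = 1, so that each arm has an effect against control alone for every month from 1 to 24. If the omission was deliberate, state the reason and revise the sentence that defines δ_t.

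When the model is coded on months 1 to 24, also drop either the intercept or one month indicator. Correcting the limit alone leaves the design rank-deficient by one (73 columns, rank 72).

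The cost is one character in the equation, one more estimated coefficient and a note in the analysis code. The design, data collection and sample size do not change.

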##### Subgroup analyses

We will conduct several subgroup analyses to provide insights into which types of clients are most likely to benefit from the intervention. We will assess intervention impact for the following subgroups:
Those with a strong vs. weak present biasThose with a high vs. low baseline treatment adherenceThose with a high vs. low baseline intrinsic motivation to take treatment

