### Sampling and participants

We will recruit into the study 330 treatment-mature Mildmay clients. We have recruited patients at Mildmay in our previous studies without significant problems, and we have an ongoing collaboration with the medical records team that allows us to react swiftly to any problems. Indeed, we were able to recruit the target number of clients in less time than originally envisioned in previous studies.

Clinical records and the electronic database will be used to identify eligible clients. The inclusion criteria are described below. Clinic staff (rather than the study coordinator) will mine the clinic database for eligible clients, given that the client at that point has not yet consented to participating in the study. We will then recruit participants from the universe of eligible patients. This approach avoids many of the disadvantages of convenience sampling, such as the bias that may arise from sampling those most easily accessible.

Once eligible clients are identified in the database, the study team will use the next appointment as an opportunity for recruitment. Each day, the study coordinators will identify patients who are due for a visit that day and approach all those deemed eligible. Once a participant is located, the coordinator will initiate the pre-baseline visit by approaching them and inquiring whether they are interested in participating in an ongoing study. Respondents will also be informed that they will not lose their spot in the queue for seeing a provider. Patients who initially agree will be taken to a separate study room to verify their eligibility. We will then get consent from the patient to participate in the study. Once the participant gives consent, we will give them a medication event management system (MEMS) cap and instruct them to store all their HIV medication in a pill bottle with the MEMS cap attached. This MEMS cap will be used to record adherence, and participants will be asked to return with the MEMS cap at their next scheduled study visit in approximately 2–3 months, so the study team can retrieve their adherence data. These first 2–3 months of adherence data will be used as a baseline and the intervention will not begin before this follow-up visit.

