### Exclusion criteria

Clients who are not able to understand the consent and study procedures will be excluded, as will clients who speak neither English nor Luganda (the local language spoken by the large majority of people in and around Kampala). In our previous studies at Mildmay, only a small number of clients had to be excluded from study participation because of these criteria. Other exclusion criteria are whether they are in any other adherence-related study and whether they are not capable of using the MEMS cap regularly. During the first follow-up visit after recruitment (roughly 2 months after the participant is recruited), we will check the MEMS-cap usage data and exclude patients who have opened it on fewer than 30% of days, as one of the study requirements stated in the consent form is that they use the MEMS cap regularly. The participant will receive a transport refund for that visit but will be asked to return the MEMS cap and not come to the study offices anymore for study purposes. It is important to note that we interpret less than 30% adherence as inconsistent use of the MEMS cap, rather than simply poor adherence. Less than 30% true adherence is very rare. Therefore, we are not necessarily excluding those with very poor adherence, but rather those who realize after initially agreeing to use the MEMS cap that they are either not able or not willing to use it after having tested it. Other exclusion criteria include patients on any third-line treatment and those who come to the clinic outside regular working hours.

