#### Follow-up surveys

Follow-up surveys will be conducted at months 6, 12, 18, and 24. These assessments will allow us to collect several data points for each participant on mediators or moderators that we believe may be influenced by the intervention (e.g., cognitive and motivational factors). After the intervention is finished, we will continue to track the adherence of participants for 12 months to assess whether the intervention encourages adherence persistence after incentives are withdrawn.

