##### Percentage of prescribed medication taken

Our behavioral primary outcome will be electronically monitored adherence. MEMS data will be collected continuously during the 24 months of the intervention period as well as for 12 months after the intervention ends, allowing us to investigate daily adherence and its timing. We will create a variable that captures the proportion of prescribed pills that were actually taken (i.e. number of actual bottle openings divided by the prescribed bottle openings).

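### Baseline adherence, and motivation if scored as a scale, are split into high and low groups, which discards roughly a quarter to a half of the information on who benefits

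*Protocol article*

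**What the plan says.** Under Subgroup analyses, the protocol article lists three contrasts: strong against weak present bias, high against low baseline adherence, and "high vs. low baseline intrinsic motivation to take treatment". Their purpose is "to provide insights into which types of clients are most likely to benefit from the intervention". Each moderator is given as two groups, and no analysis on the original scale is mentioned.

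What the article says about measurement differs by moderator:

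- **Baseline adherence** is graded. Sampling and participants says "These first 2–3 months of adherence data will be used as a baseline", and the adherence outcome is defined as a proportion: "We will create a variable that captures the proportion of prescribed pills that were actually taken". Exclusion criteria trims the lower end, because the study will "exclude patients who have opened it on fewer than 30% of days".
- **Intrinsic motivation** comes from a named instrument ("We use the Intrinsic Motivation Inventory to examine", in Baseline survey and randomization). Its scoring is not described.
- **Present bias** is collected in the baseline survey. Its scale is not described.

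**The concern.** A two-group split treats all clients on one side of the cut as alike and separates clients just either side of it. If the benefit of the lottery rises or falls gradually with baseline adherence or motivation, the split discards part of the evidence already collected.

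The trial's rationale is that rewards work by countering present bias and flagging motivation, and the Discussion promises insight into behavioral mechanisms. The subgroup analyses are the planned quantitative work closest to that promise. With about 300 clients followed to month 12, an interaction is hard to detect even with full information.

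**Working it through.** The article gives no figure for the moderator analyses, so there is nothing to reproduce. The check asks how much a split costs.

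**Inputs from the protocol article**
- 110 clients per arm and 10% attrition per year (Sample size and power): 110 × 0.9 = 99 per arm at month 12. Pooled T1 and T2 against control is then 198 against 99.
- For the previous study, "we observed mean adherence rates of ~75% as measured by MEMS caps".
- Pre-baseline opening on at least 30% of days.

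**Assumptions**
- Two-sided 5% level and a linear interaction.
- One outcome per client with SD 25 points. The article's own 6.5-point detectable difference implies about 19, so both values are shown.
- Moderation of 6.5 or 8 points per SD of the moderator.

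**Step 1: information kept.** Under randomisation and a linear interaction, the share kept is the squared correlation between the moderator and its two-group version. For a normal score cut at the median this is 2/π = 0.637, so 36% is lost and 297 clients act like 297 × 0.637 ≈ 189.

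Adherence is represented by beta distributions with mean 0.75–0.80 and SD 0.15–0.25, truncated at 0.30.

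| Moderator and cut | Information lost |
|---|---|
| Normal, median | 36% |
| Normal, quartile | 46% |
| Uniform, median | 25% |
| Adherence-like, median | 33–38% |
| Adherence-like, lower third or lower quartile | 24–35% |
| Adherence-like, upper third or upper quartile | 47–69% |
| Adherence-like (mean 0.75, SD 0.20), cut at 80% / 85% / 90% | 32% / 41% / 54% |
| Equally spread ordinal, 3–5 levels | 20–50% |
| Already binary | 0% |

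**Step 2: power at month 12, normal moderator.** The standard error of the interaction per SD of the moderator is SD × √(1/99 + 1/198) = SD × 0.1231. Power is approximately Φ(effect/SE − 1.96). A median split multiplies effect/SE by √(2/π) = 0.798.

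- SD 25, so SE 3.08. For 6.5 points per SD: 6.5/3.08 = 2.11, power 56%; after the split 1.69, power 39%.
- SD 25, 8 points per SD: 8/3.08 = 2.60, power 74%; after the split 2.07, power 55%.
- The pooled detectable difference of 6.5 points implies SD = 6.5/(2.80 × 0.1231) ≈ 18.9. For 6.5 points per SD: 2.80, power 80%; after the split 2.24, power 61%.

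Simulation agrees. With SD 25, robust standard errors and 4,000 runs, power was 57–64% continuous against 39–43% split (6.5 points), and 75–80% against 56–60% (8 points), depending on the assumed correlation between moderator and outcome. An interaction sized for 80% power gave 79% against 59%. The loss is roughly 17–21 percentage points.

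**The case against.** **Linearity.** Every loss above assumes a linear gradient, which favours the continuous term. The trial gives reasons for doubt. T2 eligibility turns on a 90% threshold, and clients who already adhere well have little room to improve. With a threshold or ceiling a split can lose less. This stands, and is why the fix includes a non-linearity check.

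**Inputs.** The SD, the moderation sizes and the moderator distributions are assumptions. Moderation of 6.5 points per SD equals the whole pooled effect the trial is sized to detect at month 12, which is large. The calculation uses one outcome per client, whereas Eqs. 3 and 4 use monthly data. This stands for the absolute power figures. It matters less for the share of information lost: a baseline moderator is constant within a client, so repeated months change the residual variance rather than that share.

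**Level of detail.** A journal article may leave cut-points and the exact interaction model to the analysis plan, and this list does not forbid a continuous analysis. That is right, and the absent cut-points are not part of this point. But the form of each moderator is stated, as two groups, and a plan that follows it would split a graded variable.

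**Stronger readings that a reader might infer**
- That all three moderators are measured on continuous scales. The article does not show this for present bias. The Background speaks of clients who display it, which reads as yes/no; the strong/weak wording suggests grading without establishing it.
- That at least a third of the information is always lost. A uniform score cut at the median, or left-skewed adherence cut low, loses about a quarter.
- That present bias might be taken after randomised treatment has begun, because Follow-up surveys mentions "mediators or moderators that we believe may be influenced by the intervention". The article places present bias in the baseline survey and does not say that follow-up values define the subgroups.

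**Conclusion.** The point holds for baseline adherence, and for intrinsic motivation if the inventory is scored as a scale. Given a roughly linear gradient, the planned split discards about a quarter to a half of the information on effect modification at ordinary cuts, with 36% as the reference value for a normal score at the median, and can discard more at a high cut. The power cost of roughly 17–21 percentage points illustrates this under assumed inputs; it is not a property that the documents fix. For present bias the size cannot be stated, and may be zero.

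These are supporting analyses. The arm comparisons on viral suppression and adherence are unaffected, so this is a cheap improvement and no threat to the trial's main conclusions.

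**What to change.** In Subgroup analyses, make the main moderation test an arm-by-moderator interaction on the measured scale for baseline adherence and the motivation score, and for present bias only if it is graded. Add these terms to Eqs. 2 and 4. Baseline adherence is already among the covariates; motivation and present bias are not, so their main effects must be added too.

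Include a simple non-linearity check, such as a quadratic term, because a ceiling or the 90% eligibility threshold could bend the gradient. Report estimated effects at low, middle and high moderator values, as risk differences for viral suppression, and keep the high/low groups for display.

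The cost is a change of wording and slightly more analysis work, with no new data. The downside is reliance on an approximately linear gradient, which the check addresses.
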